### Secondary endpoints

After 6–8 months of intervention (at around 1 year of age):
IgE-mediated food allergy determined with level 1 to at least one of the four foods HE, CM, PN, and HNIgE-mediated food allergy determined with level 1, 2 or 3 to at least one of the four foods HE, CM, PN, and HNIgE-mediated food allergy determined with level 1 or 2 to at least one of the three foods HE, PN, and HNIgE-mediated food allergy determined with level 1 or 2 to HEIgE-mediated food allergy determined with level 1 or 2 to CMIgE-mediated food allergy determined with level 1 or 2 to PNIgE-mediated food allergy determined with level 1 or 2 to HNIgE-mediated food allergy determined with level 1, 2, or 3 separately to HEIgE-mediated food allergy determined with level 1, 2, or 3 separately to CMIgE-mediated food allergy determined with level 1, 2, or 3 separately to PNIgE-mediated food allergy determined with level 1, 2, or 3 separately to HNNumber of food allergies (2, 3, 4, 5, > 6)Occurrence (frequency and severity) of immediate type allergic symptoms during the whole study periodOccurrence of gastrointestinal symptoms during the whole study periodGrowth during the whole study periodChange of eczema status (measured by SCORAD (Scoring atopic dermatitis)) after 6, 12, and 18 weeks and 6 months of intervention and at oral food challenge in those subjects who are sensitized against food allergens after 6 months of interventionChange of eczema status (measured by EASI score (Eczema Area and Severity Index)) after 6, 12, and 18 weeks and 6 months of intervention and at oral food challenge in those subjects who are sensitized against food allergens after 6 months of interventionChange in topical eczema treatment after 6, 12, and 18 weeks and 6 months of intervention and at oral food challenge in those subjects who are sensitized against food allergens after 6 months of interventionWheezing after 6, 12, and 18 weeks and 6 months of intervention and at oral food challenge in those subjects who are sensitized against food allergens after 6 months of interventionAllergen-specific IgE and IgG4 to HE, CM, PN, HN, Ara h2, Cor a14, and wheat after 6 months of intervention (at around 1 year of age)

### Randomization, allocation concealment, and blinding

After enrolment, participants will be randomly assigned to the active or placebo group in a 2:1 manner. The randomization will be prepared by the trial statistician and will be implemented within the REDCap (Research Electronic Data Capture) database system by the data manager. The randomization will include a technical stratification regarding singleton/twin status. Singletons will be assigned to the treatment groups by simple randomization in a 2:1 manner (active: placebo). Twins will also be randomly assigned to the treatment groups in a 2:1 manner (active: placebo); however, twins will be randomized together, i.e., each pair will be randomized into the same treatment group. Thus, the ratio of 2:1 will be implemented on the pair-level. In addition, the randomization of twins will be blocked (block length: 3 pairs (i.e., 6 subjects)) due to the low number of twins expected in this study. The rationale for randomizing twins into the same treatment group is the difficulty for parents to ensure the strict separation of the daily (blinded) feeding products to their infants over the course of 6–8 months. Study investigators, all involved study staff, and the parents of the participants are blinded to treatment. Allocation of subjects will be performed concealed (i.e., without knowledge of group allocation) by authorized site personnel using REDCap where each participant will be allocated to one out of fifteen kit codes for the interventional product (10 codes active, 5 codes placebo). The product will be labeled with the kit codes by staff, which is unblinded, but not otherwise involved in the study.

In general, unblinding per subject will be performed at the individual end of the study (if the patients are sensitized to HE, CM, PN, or HN at V5, they are instructed to continue consuming the study product until V6 takes place.) In case of serious allergic reactions suspected to be related to the study intervention, unblinding should be performed on the decision of the investigator. In order to ensure the unblinding process, emergency envelopes, providing information on the individual interventional group the subject is assigned to, are stored at the study center. Once unblinding has been performed, it will be documented in the source data, reported to the principal investigator and will result in the subjects’ early discontinuation of intervention.

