### Sample size calculation

Analyzing 120 infants (80 in the active group and 40 in the placebo group) will result in at least 80% power to detect a difference in the primary endpoint (food allergy after 6–8 months of intervention) of 10% in the intervention group vs. 33% in the control group, based on a two-sided chi-squared test with significance level 5%. In order to compensate for a potential dropout-rate of about 20%, 150 infants will be randomized (100 infants to the active group and 50 infants to the placebo group). As the number of twins included to this study is expected to be very low (i.e., one or two pairs), the correlation due to twin status is not taken into account for the sample size calculation.

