## Trial status

This is an abridged protocol based on protocol version 4.0 dated 05 April 2021.

The first patient was randomized in February 2020, and the last patient is planned to be enrolled in February 2023.

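### Fifteen kit codes shared by about 150 infants, with unblinding at each infant's own study end, make the arm inferable for up to about 87–90% of infants before their final assessment unless access is restricted

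*Protocol article*

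**What the plan says.** All of the blinding rules are in the protocol article under Randomization, allocation concealment, and blinding. Investigators, involved staff and parents are to be blind. Site staff allocate through REDCap, where "each participant will be allocated to one out of fifteen kit codes for the interventional product (10 codes active, 5 codes placebo". Unblinded staff with no other part in the study put the codes on the product.

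The same section then states: "In general, unblinding per subject will be performed at the individual end of the study". A sensitized infant stays on product until the food challenge at V6, so the individual end is V5 or V6. Unblinding is also allowed after a serious allergic reaction suspected to be related to the product, using individual emergency envelopes.

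Two other sections set the scale. Under Sample size calculation, "150 infants will be randomized (100 infants to the active group and 50 infants to the placebo group". Under Trial status, "The first patient was randomized in February 2020, and the last patient is planned to be enrolled in February 2023". The trial has one centre, and outcome assessment follows 6–8 months of intervention.

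**The concern.** A code tied to one arm and shared by about ten infants cannot be opened for one infant alone. The emergency envelopes are individual, which suggests that the intent was to reveal one infant at a time; shared codes defeat that. Because routine unblinding is rolling and not held until the last infant or database lock, codes start to open early and stay in use for infants who are on treatment or who enrol later.

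Several steps could be influenced by an inferred arm:

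- retention calls, and encouragement of sensitized infants' families to attend the challenge to which they are invited. The primary analysis does not impute missing outcomes, so attendance that differs by arm would bear on the odds ratio;
- changes to the intervention after adverse events, which are left to the investigator's discretion;
- classification of reactions, including accidental reactions that count as level 2 of the primary endpoint;
- SCORAD and EASI scoring, which feeds exploratory secondary endpoints, and worsening of eczema, which is an adverse event of interest.

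**Working it through.** **The plan's own figures.** "Analyzing 120 infants (80 in the active group and 40 in the placebo group) will result in at least 80% power", for event rates of 10% and 33% and a two-sided 5% chi-squared test. Recomputed power for 80 and 40 infants is 85.2% (normal approximation), 86.2% (exact, uncorrected chi-squared), 81.1% (with Yates correction) and 83.1% (Fisher), so the statement holds. Dropout inflation is 120/(1 − 0.20) = 150, as stated. The sample size is sound and this point does not affect it.

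**Inputs from the article.** 15 codes (10 active, 5 placebo); 150 infants randomized (100 and 50); 120 analysed; recruitment over about 36 months; assessment after 6–8 months.

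**Infants per code.** Active 100/10 = 10; placebo 50/5 = 10; overall 150/15 = 10.

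**Share exposed before own study end.** On each code, only the first infant to finish has no earlier-unblinded infant on the same code. Hence

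share exposed = (N − codes used)/N.

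With equally likely codes, the expected number used is 15 × (1 − (14/15)^N).

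- N = 150: 14.9995 codes used; (150 − 15)/150 = 135/150 = 90.0%.
- N = 120, if only completers count and open codes: 14.996 codes used; (120 − 15)/120 = 105/120 = 87.5%.

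Uneven use of the codes would not lower these shares: no more than 15 infants can be first on a code.

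**Timing, by simulation.** Assumptions: uniform recruitment, V5 at 6 months, V6 0.25–2 months later in the sensitized, 50% sensitized (the Background says about half). The table gives the share of infants whose code had already been opened.

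| Scenario | At randomization | By own V5 | By own end | Sensitized, by V6 |
|---|---|---|---|---|
| 36 months, 150 infants | 72.0% | 88.6% | 90.0% | 91.4% |
| 80% complete | 69.5% | 86.1% | 87.5% | 88.9% |
| Unblinding one month late | 69.0% | 85.8% | 87.4% | 88.9% |
| 33% sensitized | 72.4% | 89.1% | 90.0% | 92.0% |
| 67% sensitized | 71.4% | 88.0% | 90.0% | 90.9% |
| 24 months' recruitment | 63.0% | 87.9% | 90.0% | 92.0% |
| 48 months' recruitment | 76.5% | 88.9% | 90.0% | 91.2% |

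The share by own end hardly moves. The share at randomization depends on the assumed recruitment pattern and is only indicative.

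**The case against.** The strongest reply is that inferable is not known. The 87–90% is a counting identity. For an arm to become known, someone must link an opened infant to a code and then to another infant. The article does not say who carries out routine unblinding, who is told, whether assessors see the codes, or whether opened codes are retired. It is an abridgement of protocol version 4.0, which may restrict access. This stands as a limit on the conclusion. It does not remove the point: the article states both shared codes and rolling unblinding, and at a single centre where site staff handle the codes the link is a realistic one.

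Three stronger readings are tempting, and the article does not support them.

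- A reader might infer that each infant's arm is routinely recorded in source data and reported to the principal investigator at study end. That sentence follows the text on emergency envelopes and says that the intervention is then stopped early, which cannot apply to an infant who has finished. It most naturally describes emergency unblinding, and it records that unblinding took place, not which arm was found.
- A reader might infer that the arm of infants not yet randomized is exposed. They have no code yet. Singletons are assigned by simple randomization in REDCap, so allocation is not predictable; the weakness concerns masking after assignment.
- A reader might infer that parents can compare codes. Nothing shows that they see other infants' codes.

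The primary endpoint also has real protection. Entry to the challenge depends on specific IgE or skin prick test, level 2 needs objective systemic symptoms plus sensitization, and the challenge is double-blind with standardized stopping criteria. That blinding hides the challenge food and not the trial arm, so the protection is partial.

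**Conclusion.** The point holds as a weakness of masking. Followed as written, the scheme makes the arm inferable for up to about 87–90% of infants before their own final assessment: 90.0% if all 150 finish and are unblinded, 87.5% with 120 completers, and 87.4% if unblinding comes a month late. This assumes that codes stay in use after being opened and that no restriction on access applies beyond what the article states. An emergency unblinding opens the whole code in the same way.

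The article does not show that staff know these arms or that any outcome has been biased, and no size of bias can be derived from it. What it does show is a stated procedure that undercuts the double blind, which is a headline feature of the design and can be protected cheaply.

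**What to change.** For infants still on treatment or yet to enrol, have the unblinded labelling staff issue a unique code for each infant or twin pair and relabel the stock in use. Any unblinding then reveals only that infant or pair. Emergency unblinding stays as it is.

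Give routine end-of-study disclosure to families through the same unblinded staff and keep it out of records that assessors can see. The alternative is to hold disclosure until the last infant's final assessment. With recruitment from February 2020 to February 2023 and similar follow-up for first and last infants, that could mean a wait of about three years for the earliest families, so the separate channel is preferable.

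The cost is relabelling, a REDCap code-list update, a short amendment and the separate channel.

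For infants already assessed, report how many had their V5 or V6 after their code had been opened. A sensitivity analysis by code-opened status is not worth adding. Under the current scheme the unexposed group is about 15 infants, roughly 10 active and 5 placebo, which at the planning rates is 10 × 0.10 = 1 event and 5 × 0.33 = 1.65 events. If relabelling enlarges that group, the comparison is confounded with calendar time. If full protocol version 4.0 already restricts who can link codes to opened infants, stating that restriction would answer most of the point.

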### Study procedures

Screening (visit 1, V1) of the subjects will take place at 4–8 months of age in infants who developed eczema. Written informed consent will be obtained from the parents by the study physician. During V1, the inclusion and exclusion criteria will be checked. Subjects who are eligible for participation in the study will be randomized to one of the two study groups. Information on demographics, subject/family characteristics, relevant medical history, medication, and nutrition will be recorded. In addition, anthropometric measurements and physical examination will be performed, including the assessment of eczema severity using SCORAD [20] and EASI score [21]. Blood from the participant and its mother will be drawn. Skin swabs and saliva samples will be collected for the mechanistic subprojects by the study staff. Skin swabs are collected and preserved in DNA/RNA shield collection tubes containing medium (DNA/RNA Shield; Zymo Research, Irvine, CA, USA). Saliva samples are collected both with Zymo Swabs as well as with Salimetric Swabs (SalivaBio Swab; Suffolk, Great Britain). Transepidermal water (TEWL) measurement will be performed with the Tewameter TM Hex (Courage + Khazaka electronic GmbH, Germany). Palmar linearity pattern will be analyzed and documented by palm photographs.

The investigator will instruct the parents to collect stool samples (using OMNIgene-GUT tubes, OMR-200; DNA Genotek, Ontario, Canada) from the infants at home for the mechanistic subprojects. The parents should further collect a dust sample (using dustream® collector DU-ST-1; Indoor Biotechnologies LTD, Cardiff, UK) from the infant´s bed (or the parent´s bed, if the child sleeps in this bed four nights or more per week) and the living room.

The first feeding of the study product will be performed at the study site. Parents will be asked to maintain an e-diary from V1 to V5/V6. The e-diary contains questions concerning the patient´s diet, compliance, and tolerability of the study product, eczema severity (POEM score [22]) and concomitant medication.

Supplies of study product will be dispensed at each visit. Parents will be instructed to contact the study site in case of an immediate type allergic reaction after food exposure (either to the study product or due to exposure to any food allergens). Additionally, in case of recurrent gastrointestinal symptoms, worsening of eczema or any suspected adverse event parents are asked to contact the study site. Two weeks after V1, parents will be called (phone call 1; PC1) to investigate compliance and tolerability of the study product and to promote retention. Subjects will be required to visit the study site after 6 (V2), 12 (V3) and 18 (V4) weeks, and 6 (V5) months of intervention. At V2, V3, V4, and V5, information on medical history, medication (especially treatment of eczema), and nutrition (breast feeding, complementary foods) will be recorded. In addition, anthropometric measurements and a physical examination including SCORAD and EASI score will be performed. Stool, dust, skin swabs, and saliva samples will be collected. TEWL will be performed. At V2, V3, and V4, the first feeding of the next higher dose of the verum, respectively of the placebo in order to ensure blinding, will be performed at the study site. Supplies of study product will be dispensed at each visit. Two weeks after V2, V3, and V4, parents will be called (PC2, PC3, and PC4) to investigate compliance and tolerability of the study product. An additional blood sample from the participant and its mother will be collected, and a SPT with HE, CM, PN, and HN will be performed at V5 (all extracts including positive and negative controls: ALK Abelló, Germany). Participants sensitized to any of the checked foods (elevated food-specific IgE (> 0.1 kU/l) or positive SPT (wheel size > 3 mm)) will be invited to undergo an OFC at V6. Sensitized patients are instructed to continue consuming the study product until V6 will take place. OFC will be performed in a double-blinded, placebo-controlled manner in accordance with clinical routine practice of the Charité-Universitätsmedizin Berlin, based on PRACTALL international guidelines for OFC and stopped using standardized stopping criteria based on PRACTALL guidelines [23]. Roasted, defatted peanut flour, defatted HN flour, fresh CM, and pasteurized raw HE will be used for OFC. Up to seven increasing dose steps at 30-min intervals using a semi log scale ranging approximately from 2 mg to 3 g food protein (depending on the individual allergen) will be administered. In case of absence of any objective, allergic symptoms, a cumulative dose up to 4.5 g food protein will be administered on another day. In patients with allergic reactions to raw HE and fresh CM, an additional food challenge will be offered with baked HE or CM, respectively. Participants who developed a clinical relevant food allergy at the end of the trial will receive an individualized dietary counseling. Moreover, parents are offered to contact the outpatient clinic of the Department of Pediatric Pulmonology, Immunology and Critical Care Medicine, Charité – Universitätsmedizin Berlin, for further consultation. In case of discontinuation or deviation from the intervention protocol, all participants are encouraged to maintain the scheduled visits or phone calls and collection of all possible data is planned. For detailed description of all study procedures, see Table 2.

**Table 2 Tab2:**
[figure not shown]
Study visits and procedures

*Abbreviations*: *V* visit, *PC* phone call, *AE* adverse event, *TEWL* transepidermal water loss measurement, *SPT* skin prick testing, *OFC* oral food challenge

### Data collection and management

REDCap (Research Electronic Data Capture) will be used as electronic case report form (eCRF) to collect and manage study data. REDCap is hosted at the Charité – Universitätsmedizin Berlin and provides an interface for data entry for clinicians. In addition, it provides a data integration platform for the data from the mechanistic subprojects. Audit-trails will be integrated for tracking data entries, corrections, and import/export procedures. A unique participant number will be assigned to every screened patient consisting with a prefix and a consecutive numbering. This unique code will identify all patient-specific data, e.g., clinical study data as well as biosample results. Any adverse event will be documented on paper documents (diary). Adverse events of interest (recurrent gastrointestinal symptoms, worsening of eczema and allergic reactions) as well as serious adverse events (SAEs) will be additionally documented in the REDCap eCRF. In case of any adverse of interest, parents are advised to contact the study site as soon as possible. SAEs have to be reported within 48 h after knowledge of event to the principal investigator. Data access and storage will follow the data security concept of the Charité including password-protected access to all computers and folders, which contain sensitive data. Pseudonymized data will be made available to all groups participating in the CRU.

### Sample size calculation

Analyzing 120 infants (80 in the active group and 40 in the placebo group) will result in at least 80% power to detect a difference in the primary endpoint (food allergy after 6–8 months of intervention) of 10% in the intervention group vs. 33% in the control group, based on a two-sided chi-squared test with significance level 5%. In order to compensate for a potential dropout-rate of about 20%, 150 infants will be randomized (100 infants to the active group and 50 infants to the placebo group). As the number of twins included to this study is expected to be very low (i.e., one or two pairs), the correlation due to twin status is not taken into account for the sample size calculation.

### Statistical analysis

The primary analysis of the primary endpoint will be performed by logistic regression with (fixed) factor treatment group (active, placebo) taking the correlation of twins into account. From this model, the odds ratio for treatment will be calculated with 95% confidence interval and a *p*-value for the treatment group comparison. The analysis will be performed on the full analysis set (FAS) without imputation of missing values. The significance level will be set to 0.05 (two-sided). All other analysis will be considered explorative. Several explorative sensitivity analysis will be performed for the primary endpoint: a re-run of the primary analysis model without taking the correlation of twins into account and a re-run of the primary analysis model with the per- protocol population (instead of the FAS). In case of relevant differences between the treatment groups with respect to baseline variables, the primary analysis will be repeated with further adjustment variables (FAS population). Moreover, several subgroup analysis will be conducted regarding the following subgroups: carrier of mutations in the Filaggrin gene; infants with at least one parent with eczema; infants with at least one parent with atopic diseases (asthma, rhinoconjunctivitis, eczema); breastfed children/formula fed children, children with impaired skin barrier function (measured with TEWL); and household allergen exposure. Subgroup analysis will be performed by additionally including the subgroup variable and the interaction term (subgroup*treatment group) into the primary analysis model (FAS population). In case subpopulations regarding to the consumption of CM exist, these subpopulations will be analyzed separately (FAS population).

Explorative analysis of secondary endpoints will follow the same principle as the primary analysis of the primary endpoint, i.e., models with (fixed) factor treatment group, taking the correlation of twins into account. Binary endpoints will be analyzed by logistic regression; continuous endpoints will be analyzed by analysis of covariance (ANCOVA) with the respective baseline value (if available) as additional covariate. Secondary endpoints will be analyzed with the FAS; selected secondary endpoints will also be analyzed with the per-protocol population. Concerning safety endpoints, the nature, frequency, and severity of adverse events and safety variables, including serious adverse events, will be summarized descriptively by treatment group. As a general strategy, missing data will not be imputed in this study. No interim analyses for efficacy are planned.

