### Primary endpoint

The primary endpoint is the occurrence of IgE-mediated food allergy determined with level 1 or 2 to at least one of the four foods (HE, CM, PN or HN) after 6–8 months of intervention (at around 1 year of age).

The diagnosis of food allergy will be determined according to the following levels:
Level 1: A positive oral food challenge at around one year of age in a child with allergen-specific IgE > 0.1 kU/l or skin prick test (SPT) wheel size > 3 mm.Level 2: A systemic reaction with objective symptoms upon accidental exposure in a child with specific IgE to one of the four intervention foods > 0.1 kU/l or SPT wheel size > 3 mm.Level 3: Allergen- or allergen component-specific IgE above the 90% predicted probability for this individual food [18, 19].

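### After V5, a primary outcome can be missing essentially only in sensitised infants without a completed challenge, and the plan has neither imputation nor a missing-outcome sensitivity analysis for them

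*Protocol article*

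**What the plan says.** Under Primary endpoint, an event is Level 1 or Level 2 to at least one of four foods. Level 1 is a positive oral food challenge in a sensitised infant. Level 2 is an objective systemic reaction on accidental exposure, also in a sensitised infant. Level 3, "Allergen- or allergen component-specific IgE above the 90% predicted probability for this individual food", does not count towards the primary endpoint. It enters only exploratory secondary endpoints.

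Under Study procedures, infants sensitised at V5 "will be invited to undergo an OFC at V6". The legend of Fig. 1 says that the intervention stops in non-sensitised infants, and no challenge is foreseen for them.

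Under Statistical analysis, the rule for the primary model is: "The analysis will be performed on the full analysis set (FAS) without imputation of missing values". It is repeated for the whole study: "As a general strategy, missing data will not be imputed in this study". The sensitivity analyses named for the primary endpoint are a model that ignores twin correlation, a per-protocol analysis and, if the groups differ at baseline, an adjusted model. None of them varies how missing outcomes are handled.

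**The concern.** Whether an infant has an observed primary outcome after V5 depends on a post-randomisation result, sensitisation, that is closely tied to the outcome. A non-sensitised infant is fully classified at V5. A sensitised infant whose family declines or does not complete the challenge is unclassified, unless a Level 2 reaction has occurred. With no imputation, the natural reading is that this infant drops out of the model. The infants removed are then those at highest risk, while every non-sensitised infant stays in.

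At stake is the only confirmatory test in the trial. The two arm rates, which readers will quote, would be too low. If families in the two arms decline at different rates, the odds ratio and its p-value are affected too, and nothing in the named analyses would reveal it. A difference is conceivable because only active infants can react to the four allergens in the product.

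**Working it through.** **1. The plan's own figure.** Sample size calculation: "Analyzing 120 infants (80 in the active group and 40 in the placebo group) will result in at least 80% power" for a difference "of 10% in the intervention group vs. 33% in the control group", two-sided 5% chi-squared test. Pooled rate = (80×0.10 + 40×0.33)/120 = 0.177. Standard error under the null = √[0.177×0.823×(1/80 + 1/40)] = 0.0739; under the alternative = √(0.10×0.90/80 + 0.33×0.67/40) = 0.0816. Power = Φ[(0.23 − 1.96×0.0739)/0.0816] = Φ(1.045) = 85.2%. Dropout: 120/0.80 = 150. Both figures reproduce.

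**2. Risk in those who can be missing.** Background gives about half sensitised and about one third allergic. With s = 0.50 and p = 0.33, a sensitised infant has risk 0.33/0.50 = 66%, against 33% overall and about 0 in the non-sensitised.

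**3. Complete-case rate.** Let r be the share of sensitised infants without a completed challenge, assumed unrelated to true allergy within the sensitised. Then

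observed rate = p(1 − r)/(1 − s·r).

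The documents give neither r nor the active-arm sensitised share. Both are assumptions below.

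**4. Equal r in both arms** (true rates 33% and 10%, true OR 0.226, risk difference 23 points; placebo s = 0.50, active s from 0.15 to 0.50):
- r = 20%: placebo 0.33×0.8/0.90 = 29.3%; risk difference 20 to 21 points; OR 0.217 to 0.235.
- r = 40%: placebo 0.33×0.6/0.80 = 24.7%; risk difference 17 to 18 points; OR 0.207 to 0.247.

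Take r = 30% with active s = 0.30 and another 10% lost at random before V5. The rates are 0.33×0.7/0.85 = 27.2% and 0.10×0.7/0.91 = 7.7%, and the OR is 0.223. Simulated power is about 80%. Total loss in this case is 100×(1 − 0.9×0.91) + 50×(1 − 0.9×0.85) = 18.1 + 11.75 = 29.9 of 150, or about 20%, which is the planned dropout. The same 20% lost purely at random leaves power at about 86.5%.

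**5. Unequal r, no true effect** (33% allergic and 50% sensitised in both arms, 100/50 randomised, 10% other random loss; type I error by simulation, uncorrected chi-squared test):

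| r active / placebo | Observed rates | OR | Type I error |
|---|---|---|---|
| 30% / 30% | 27.2% / 27.2% | 1.00 | 5% |
| 20% / 10% | 29.3% / 31.3% | 0.91 | about 6% |
| 30% / 10% | 27.2% / 31.3% | 0.82 | about 8% |
| 40% / 10% | 24.8% / 31.3% | 0.72 | about 12% |

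Example, 30% / 10%: active 0.33×0.7/(1 − 0.15) = 0.272; placebo 0.33×0.9/(1 − 0.05) = 0.313; OR = (0.272/0.728)/(0.313/0.687) = 0.82.

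**6. Losses before V5.** The 20% dropout is not split by timing. If it all falls before V5 and is unrelated to sensitisation, the placebo rate stays at 33%. If half is before V5 and half is non-completed challenges, r = 0.10/(0.90×0.50) = 22%, and the placebo rate is 0.33×0.778/0.889 = 28.9%.

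**The case against.** The strongest reply has four parts.

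- **The planned estimate is an odds ratio, and equal non-completion barely moves it.** This stands. With r = 30% in both arms the OR goes from 0.226 to 0.223 and the type I error stays at 5%. Power of about 80% still meets the plan's stated minimum. The arm rates and the risk difference are nonetheless understated.
- **Large inflation of the type I error needs large gaps.** This stands too. A reader might infer that the trial runs at 12% or more. That takes at least a four-fold gap in non-completion, and in the 40% / 10% case it loses 28% of the active arm (1 − 0.9×0.80), more than the planned 20%. Sensitised infants continue the product until V6 and unblinding is generally at the individual end of study, so most families decide while blinded. Blinding makes a gap less likely but does not exclude one after reactions to the product.
- **The article is abridged.** It does not define the FAS or say how a sensitised, unchallenged infant is classified, and the full protocol or the SAP may do so. That the infant is dropped is therefore an inference. The no-imputation rule, however, is stated here twice, and an SAP consistent with it could not impute this endpoint.
- **A safeguard exists.** The Level 1, 2 or 3 secondary endpoint counts an unchallenged infant with very high IgE as an event. It is exploratory, and it leaves unresolved the sensitised, unchallenged infants below the 90% threshold.

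A reader might also infer that every missing outcome belongs to a sensitised infant. The documents do not support that: infants lost before V5 have no outcome whatever their sensitisation. Nor do they support treating an effect of the product on sensitisation as established, since sensitisation levels are themselves a secondary endpoint.

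**Conclusion.** The point holds for infants who reach V5. Among them, missing primary outcomes arise essentially only in sensitised infants, whose allergy risk is about 66% against 33% on the article's background rates. A complete-case analysis then understates both arm rates and shrinks the risk difference, for instance from 23 points to 20 or 21 at 20% non-completion. The odds ratio is nearly unaffected under equal non-completion and biased under unequal non-completion, by an amount that depends on a gap the documents do not quantify. For moderate gaps (20% or 30% vs 10%) the type I error is about 6% to 8%.

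These sizes assume a 50% sensitised share, non-completion unrelated to true allergy among the sensitised, and 10% other random loss. The documents do not show that a gap between arms will occur or which arm it would favour. What they do show is that the listed analyses could not detect one.

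**What to change.** State that an infant non-sensitised at V5 counts as a non-event for the primary endpoint. State how a sensitised infant without a completed challenge is classified. Keep the planned logistic model, but replace the blanket no-imputation rule with pre-specified sensitivity analyses of the primary endpoint for these infants:

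- (a) multiple imputation of the any-food outcome from arm, V5 specific IgE, SPT size and SCORAD;
- (b) Level 3 counted as an event where no challenge was done;
- (c) a tipping-point table by arm.

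Report challenge non-completion by arm, and report losses before V5 separately.

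The cost is protocol and SAP wording plus modest programming, and the V5 inputs are already collected. Analysis (a) assumes missing at random given IgE and SPT, which (c) is there to probe. Imputing each of the four foods separately, or making imputation the primary analysis, is harder to defend at this size: with 10% lost before V5, about 22 placebo infants would be sensitised (50×0.9×0.5 = 22.5). The any-food outcome as a sensitivity analysis is enough.
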